### Prior Work

The optical properties of the skin’s interaction with light can be evaluated by devices that emit and receive photons [13]. Variations in light scattering through the skin are believed to be associated with changes in skin thickness, the concentration of chromophores, and light wavelength [14]. A novel technology was developed to estimate GA at birth (Test-GA) by analyzing the photobiological properties of the newborn’s skin in combination with clinical variables [15]. This noninvasive and nonionizing technology features a probe containing light emitters and receivers that is brought in contact with the skin over the sole. A mathematical algorithm provides an estimated GA within seconds, combining the skin reflection with clinical adjusters, such as birth weight and incubator stay [15].

The timeline of the new medical device development involves sequential steps [16], represented in Figure 1. The prototype of the device previously evaluated 115 newborns at 24-41 weeks’ gestation with promising results [15]. After insights from this first clinical experiment published in 2017, the technology received improvements to mitigate external influences in the test, such as humidity, ambient light, and to ease the user handling. The current version is a small device, about the size of a pen, with an automated ability to measure skin reflection. To reduce examiner influence, the device now warns about errors of measurement. Clinical variables are presented in a digital screen immediately after the newborn skin assessment. Since February 2019, a clinical trial is taking place in 5 Brazilian hospitals to advance the GA prediction modeling, using a sample of 787 newborns [17]. The planned date of last enrollment is July 2020.

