### Eligibility Criteria and Participant Timeline

A sequential enrollment of newborns will follow the inclusion of participants based on eligibility criteria until the sample size is achieved. The inclusion criteria are liveborn infants weighing 500-2499 g with GA information obtained using a qualified last menstrual period or obstetric ultrasound <24 weeks’ gestation (Comparator-GA). Exclusion criteria are structural skin alterations or conditions that modify the skin, such as anhydramnios, hydrops, congenital skin diseases, and chorioamnionitis.

Table 1 illustrates the schedule of enrollment, test application, and endpoint measurement. The skin assessment will occur during the first 24 hours of age. The newborns will be followed up for 72 hours until discharge, held in hospital (for treatment-related purposes), or death, whichever occurs first, considered the study exit. The newborns will continue to receive standard assistance after the study follow-up according to settings, resources, and local staff definitions, whether during hospital admission or at hospital discharge or re-admission.

**Table 1 table1:** Participant timeline of the study.

Study procedures	Before Test-GA	Test-GA, ≤24 hours old	72 hours old: discharged, held in hospital, or death
Enrollment 1: Prospective cohort study^a,b^	X		
Informed consent	X		
Taking of obstetric history	X		
Intervention: Test-GA		X	
Comparator: Best estimation of GA available		X	
Enrollment 2: Nested case–control study^c^			X
Assessments and analysis^d^			X

^a^Inclusion criteria are liveborn, Comparator-GA (reliable last menstrual period [18] or ultrasound assessment at <24 weeks’ gestation [8]), birth weight (500-2499 g), and ≤24 hours old.

^b^Exclusion criteria are malformation with structural skin alterations and skin modifiers (eg, anhydramnios, hydrops, congenital skin diseases, chorioamnionitis).

^c^To determine eligibility criteria for paired allocation according to birth weight range to either the case group (TTN or RDS) or the control group (without TTN, RDS, tachypnea due to other reasons, or bloodstream infection).

^d^Neonatal outcomes including respiratory complications due to prematurity, neonatal intensive care unit admission, or ventilatory support

GA: gestational age; RDS: respiratory distress syndrome; TTN: transitory tachypnea of the newborn.

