Within the study cohort, a secondary nested case–control study will include newborns with the following inclusion criteria: (1) for the case group, respiratory distress syndrome or transitory tachypnea of the newborn; (2) for the control group, newborns will be randomly selected with no respiratory diseases or manifestations by other conditions, paired by birth weight range: <1000 g, 1000-1499 g, or 1500-2499 g.

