### Data Definition and Collection

Comparator-GA is calculated by obstetric data obtained at the time of enrollment. The requirements for establishing the best GA calculation (assessed by interviewing the mother) are based on the following:

reliable last menstrual period dating, including certainty about last menstrual dating, regular menstrual cycles, no contraceptives within 3 months of conception, and no abortion or delivery 2 months prior to conception [18]; ORultrasound <24 weeks’ gestation, considered reference for low-income countries as recommended by the World Health Organization (WHO) [8], even if the clinical information on last menstrual period is absent.

For data curation, pregnancy dating based on ultrasonography reports will be adjusted to Intergrowth 21 standards. Fetal crown–rump length [23] as well as femur length and head circumference will be used to recalculate GA [24]. When both ultrasound and reliable last menstrual period dating are available, correction will depend on whether there are discrepancies in excess of 5, 7, 10, or 14 days according to the identified GA at first assessment as recommended in ACOG Committee Opinion guideline number 700 (May 2017) [6].

Test-GA will be determined by statistical analysis according to signals stored in the device’s processor and clinical data. For this, the GA modeling prediction is based on the result of another ongoing clinical trial (registration number RBR-3f5bm5). This study is taking place at 5 Brazilian centers with the analysis of the skin reflection and clinical data of 787 newborns, with 24-42 weeks of gestation, using strict rules of the crown–rump length ultrasound measurement for pregnancy dating [17]. We expect to establish the prediction model toward the end of the RBR-3f5bm5 clinical trial in September 2020.

Birth weight is the first measurement performed by the local staff during the first 24 hours of life. A digital scale for standardizing weighing is already present in all settings.

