#### Secondary Outcomes

The secondary endpoint will be the proportion of correctly identified SGA newborns under the tenth percentile of GA according to Intergrowth 21 standards [25]. For this endpoint, the proportion of SGA newborns detected by the Test-GA will be compared with that detected by the Comparator-GA.

Others secondary endpoints in the case–control nested study will be the capacity of the Test-GA results to predict the following neonatal complications:

Respiratory distress syndrome based on clinical and radiological findings and respiratory outcomes [26,27].Transitory tachypnea of the newborn based on clinical findings and respiratory outcomes [26].Ventilatory support due to pulmonary immaturity.Neonatal intensive care unit admission for pulmonary immaturity.

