### Statistical Analysis

To assess differences between the Test-GA and Comparator-GA estimates, average difference (with standard deviations), intraclass correlation coefficient, paired *t*-testing, and Bland–Altman scatter plots [30] will be used. To evaluate the accuracy of Test-GA in identifying preterm and SGA neonates, sensitivity, specificity (with 95% confidence intervals), and receiver operating characteristic curves and other discriminant analysis techniques will be calculated. The relationship between the measurement of the newborn’s skin reflectance and newborn’s respiratory complications due to immaturity will be evaluated using receiver operating characteristic curves, association tests, and risk ratios. The significance level for hypothesis tests will be 5%, together with 95% confidence intervals.

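### Pairing controls on birth weight, an input of Test-GA, means an unadjusted AUC from the nested study would not estimate respiratory discrimination in the low-birth-weight cohort; no step for the pairing is stated

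*Protocol article*

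**What the plan says.** Eligibility Criteria and Participant Timeline defines the nested study. Cases are "for the case group, respiratory distress syndrome or transitory tachypnea of the newborn". Controls are a random selection of cohort members, "paired by birth weight range: <1000 g, 1000-1499 g, or 1500-2499 g". Note c to Table 1 narrows the pool further, to a "control group (without TTN, RDS, tachypnea due to other reasons, or bloodstream infection". No matching ratio is given.

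Prior Work describes the GA algorithm as "combining the skin reflection with clinical adjusters, such as birth weight and incubator stay". Data Definition and Collection leaves the final model to the companion trial but keeps both kinds of input: "Test-GA will be determined by statistical analysis according to signals stored in the device’s processor and clinical data".

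Secondary Outcomes places the respiratory endpoints in the paired sample and names Test-GA as the marker: "Others secondary endpoints in the case–control nested study will be the capacity of the Test-GA results to predict the following neonatal complications". The complications listed are RDS, TTN, ventilatory support and NICU admission. Statistical Analysis names another marker: "The relationship between the measurement of the newborn’s skin reflectance and newborn’s respiratory complications due to immaturity will be evaluated using receiver operating characteristic curves", followed by association tests and risk ratios. The Abstract (Methods) and the secondary objective also refer to skin reflection. None of these sections says how the pairing enters the analysis.

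**The concern.** The article's aim, in the Abstract and again in the Discussion, is to predict respiratory problems in low-birth-weight newborns as they present. That is a cohort question. In the nested sample, however, the weight distribution of the controls is made equal to that of the cases, and weight is part of Test-GA. Some of the separation that Test-GA would show in the cohort is thus removed by design. An ordinary ROC curve on these data gives neither the cohort AUC nor the AUC within a weight band.

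Risk ratios raise a related problem. The share of cases in a paired sample is set by the matching ratio and not by incidence, so the sample proportions are not risks.

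What is at stake is how the respiratory accuracy result can be read. A reader would take a reported AUC as performance in the target population, which it would not be.

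**Working it through.** **The plan's own figure.** The only size given is 298, for detection of prematurity. It is the smallest n for which the one-sided 95% exact binomial lower limit reaches 0.90 with probability at least 0.95 when true accuracy is 0.95 (the probability is 0.928 at n = 297 and 0.954 at n = 298). The 0.95 accuracy, the one-sided limit and the 0.95 probability are inferred. This figure has no bearing on the nested study, for which the article gives no number of cases, matching ratio or expected AUC.

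**Direction of the matching effect.** Let p_j be the share of cases in weight band j, q_k the share of eligible non-cases in band k, and A_jk the probability that a case from band j has a lower Test-GA than a control from band k.

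- Cohort AUC (eligible non-cases) = Σ p_j q_k A_jk
- Unadjusted paired AUC = Σ p_j p_k A_jk, because pairing replaces q by p
- Within-band AUC (case-weighted) = Σ p_j A_jj
- Cohort minus paired = Σ p_j (q_k − p_k) A_jk

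A_jk rises with k, because heavier controls have higher Test-GA. If cases are lighter than non-cases, q puts more weight on the heavy bands than p does, so the last line is positive. Weighting each control by q_k/p_k restores the first line.

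**Size.** The documents give none of p, q or A, so every input here is an assumption. Simulated cohort of 500–2499 g: GA normal, mean 34 and SD 3.2 weeks; log-weight SD 0.15 around an assumed growth curve; skin signal equal to GA plus error of SD 1.8 weeks; Test-GA the regression of GA on skin signal and weight; risk of RDS or TTN logistic in GA, 50% at 33 weeks, slope −0.55 per week. The later cohort uses GA mean 36 and SD 2.5. The weak link uses slope −0.3 with 50% risk at 31 weeks. The strong link uses slope −0.9 with 50% risk at 30 weeks. AUC of Test-GA, with no exclusion of ill controls:

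| Scenario | Cohort | Paired, controls reused | Paired 1:1, no reuse | Loss |
|---|---|---|---|---|
| Base | 0.759 | 0.604 | 0.661 | 0.156 / 0.099 |
| Later cohort | 0.703 | 0.644 | 0.663 | 0.059 / 0.040 |
| Later cohort, weak link | 0.629 | 0.590 | 0.592 | 0.039 / 0.037 |
| Strong link, fewer cases | 0.864 | 0.618 | 0.644 | 0.245 / 0.220 |

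Losses were computed before rounding. They run from about 0.04 to 0.25. For the skin signal alone the same scenarios give 0.025 to 0.161. Reweighting controls by band in the base case returns 0.759, the cohort value.

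**Control exclusions.** Suppose 15% or 30% of non-cases at 34 weeks, and more at lower GA, are dropped as controls for other illness. The Test-GA loss against all real non-cases is then 0.003 to 0.236. In the later cohort with a weak link and 30% dropped it is 0.013 or 0.003, and for skin alone 0.001 or −0.003.

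**Precision.** The 95% half-width of an AUC of 0.6 to 0.8 (Hanley–McNeil) is 0.087 to 0.111 with 50 pairs and 0.061 to 0.078 with 100 pairs. The smaller losses lie within this.

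**Risk ratios.** In one band, let a and c be cases with and without a positive marker, b and d the sampled controls, and f the fraction of eligible non-cases sampled. The cohort ratio is [a/(a + b/f)] / [c/(c + d/f)]; the sample gives [a/(a + b)] / [c/(c + d)]. If the marker is associated with the outcome, the two agree only when f = 1, and f differs between bands.

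**The case against.** A reader might infer that the plan pools all pairs into one ROC curve and that the resulting AUC will be far below the true value. The documents do not support either statement. Statistical Analysis says neither pooled nor stratified, and such detail may sit in an analysis plan that is not shown. How far below depends on the weight mix and on the strength of the link between GA and respiratory illness, and the article gives neither. The control exclusions work the other way, so even the sign of the net bias is not assured. No AUC target is stated either, so nothing shows that a respiratory claim would be wrongly dropped.

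The second objection concerns the marker. Birth weight is not an input of skin reflectance, which is the marker named in Statistical Analysis. For that marker, pairing on weight is a recognised way to ask what the skin adds to weight, and the weight-conditional AUC is a legitimate quantity.

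Both objections limit the claim but do not remove it. The article itself fixes the pairing and places prediction by Test-GA inside the paired sample, and it lists risk ratios for data selected on outcome. The beyond-weight reading does not fit Test-GA, which is described as containing weight, and the two sections disagree on which marker is meant. Two opposing biases of unknown size do not make the AUC interpretable for the cohort.

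**Conclusion.** The point holds in a limited form. An unadjusted AUC from the paired sample would not estimate the discrimination of Test-GA in the low-birth-weight cohort. Taken alone, the matching lowers it, provided cases are lighter than non-cases, which is to be expected for complications of prematurity. Under the assumed scenarios the loss is about 0.04 to 0.25. With the control exclusions added it is about 0.00 to 0.24. These ranges illustrate the effect and do not predict this trial's result. They rest on birth weight remaining in the final Test-GA model, which is not yet fixed, and they cover RDS or TTN only; ventilatory support and NICU admission were not simulated.

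Two parts need no simulation: risk ratios cannot be taken directly from outcome-selected pairs, and the endpoint and analysis sections name different markers. The severity is moderate. The endpoint is secondary, and the sample is nested in a cohort whose sampling frame is known, so the problem can be repaired.

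**What to change.** 1. State that ROC/AUC, sensitivity, specificity and risk ratios for the respiratory endpoints are estimated in the whole enrolled cohort. Table 1 plans Test-GA and 72-hour assessment there.
2. If the case–control sample must be used for these quantities, weight controls by band to the cohort non-cases. This corrects for the matching only. It does not undo the exclusion of ill controls: in the base case with 15% excluded, weighting gives 0.776 against 0.758 for all non-cases. The whole-cohort analysis is therefore preferable.
3. Keep the paired sample for a separate, labelled question: what the marker adds beyond birth weight. Use a band-stratified ROC and a regression conditional on band.
4. Reconcile Secondary Outcomes with Statistical Analysis on whether the marker is Test-GA, skin reflectance or both, and say which analysis applies to each.

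The cost is analysis wording. No further newborns, measurements or follow-up are needed, provided respiratory outcomes are recorded for every enrolled newborn, which selecting cases and controls already requires.

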### Intervention

The assessment with the device will occur as soon as possible after birth according to the detailed protocol of the skin assessment available online [19]. The device provides automatic data acquisition with minimum operator influence and stores values in an electronic database. No values will be displayed on the device screen, thereby blinding the users to the results obtained at the time of acquisition. Characteristics of the components, wavelength of the light emitter, and external acquisition for the metering process categorized the safety level of this medical device as Class II (noninvasive and medium risk) according to the regulatory agency in Brazil. The prototype unit of measurement and process of GA estimation are patented (Nos BR1020170235688 and CTIT-PN862, respectively) [20].

### Training, Roles, and Monitoring

Teams of health professionals were trained and standard operating procedures were developed following the good practice guidelines for the clinical investigation of medical devices for human participants according to the International Organization for Standardization 14155:2011 [21] and the regulatory health agency’s recommendations for the approval of medical devices [22]. The training occurred in September 2018 in Brazilian hospitals and in July 2019 in the Hospital Central de Maputo, Mozambique. Data collection and monitoring have been happening since then. All participating centers were visited by the study coordinator to qualify the clinical investigators for training in Good Clinical Research Practice, with attention paid to the requirements for validation of medical devices and the completion of at least 30 simulated examinations. Local research coordinators contributed to development of the study protocol and will supervise the data collection and record confidentiality.

### Data Definition and Collection

Comparator-GA is calculated by obstetric data obtained at the time of enrollment. The requirements for establishing the best GA calculation (assessed by interviewing the mother) are based on the following:

reliable last menstrual period dating, including certainty about last menstrual dating, regular menstrual cycles, no contraceptives within 3 months of conception, and no abortion or delivery 2 months prior to conception [18]; ORultrasound <24 weeks’ gestation, considered reference for low-income countries as recommended by the World Health Organization (WHO) [8], even if the clinical information on last menstrual period is absent.

For data curation, pregnancy dating based on ultrasonography reports will be adjusted to Intergrowth 21 standards. Fetal crown–rump length [23] as well as femur length and head circumference will be used to recalculate GA [24]. When both ultrasound and reliable last menstrual period dating are available, correction will depend on whether there are discrepancies in excess of 5, 7, 10, or 14 days according to the identified GA at first assessment as recommended in ACOG Committee Opinion guideline number 700 (May 2017) [6].

Test-GA will be determined by statistical analysis according to signals stored in the device’s processor and clinical data. For this, the GA modeling prediction is based on the result of another ongoing clinical trial (registration number RBR-3f5bm5). This study is taking place at 5 Brazilian centers with the analysis of the skin reflection and clinical data of 787 newborns, with 24-42 weeks of gestation, using strict rules of the crown–rump length ultrasound measurement for pregnancy dating [17]. We expect to establish the prediction model toward the end of the RBR-3f5bm5 clinical trial in September 2020.

Birth weight is the first measurement performed by the local staff during the first 24 hours of life. A digital scale for standardizing weighing is already present in all settings.

A double system of clinical data collection was implemented. Trained researchers will fill out paper-based formularies and an electronic interface. Original ultrasound and clinical information reports of the antenatal care will be scanned. A double-check data conference will adjust typos comparing original paper–based documents with the electronic clinical records before the statistical analysis. The system has been designed to avoid inconsistencies in typing data according to preset constraints of expected information. Recordkeeping and server backup will be performed according to informatics best practices. To guarantee anonymity, patient identification will only be accessible by the collaborating center coordinators. The data entry form is available in Multimedia Appendix 1.

### Study Outcomes

#### Primary Outcomes

The primary endpoints will be differences between the Test-GA and Comparator-GA estimates and proportion of correct preterm newborn detections by the Test-GA at <37 weeks’ gestation with a 1-week margin of error.

#### Secondary Outcomes

The secondary endpoint will be the proportion of correctly identified SGA newborns under the tenth percentile of GA according to Intergrowth 21 standards [25]. For this endpoint, the proportion of SGA newborns detected by the Test-GA will be compared with that detected by the Comparator-GA.

Others secondary endpoints in the case–control nested study will be the capacity of the Test-GA results to predict the following neonatal complications:

Respiratory distress syndrome based on clinical and radiological findings and respiratory outcomes [26,27].Transitory tachypnea of the newborn based on clinical findings and respiratory outcomes [26].Ventilatory support due to pulmonary immaturity.Neonatal intensive care unit admission for pulmonary immaturity.

### Sample Size

The sample size calculation is estimated based on the primary endpoint. Previous studies reported that Test-GA has 90%-100% accuracy at identifying premature newborns [28]. Using the inferior value of the confidence interval, an overall sample size of 298 newborns, including premature and term, is required for a robust evaluation of the device’s accuracy as recommended by Flahault et al [29].

